### 2.8. Data Collection

#### 2.8.1. Time Points

Primary and secondary outcomes will be measured at baseline (0 week), post-intervention (12+1 week) and at end point (36+1 week). The assessments will include basic demographic-socio-economic information, anthropometrics measurements, primary and secondary outcome measurements and biological sampling (see Figure 1 and Table 1).

#### 2.8.2. Baseline Assessment 

After participants’ inclusion and after their signed informed consent is obtained, baseline assessments will be conducted prior to the randomization by the trained project assistants Assessments of demographic-socio-economic characteristics, anthropometric measurements and primary and secondary outcomes (see the outcome variables section) will be conducted. It is anticipated that a total of 120 min–140 min will be required to complete all baseline assessments. If participants are not willing to give information at one sitting, the next possible dates will be discussed and assessments will be made as per the participant’s convenience.

#### 2.8.3. Post Intervention and End Point Assessments 

Post-intervention assessments and end point assessments will be conducted at 12+1 and 36+1 weeks, respectively. All assessments and blood analysis will be similar to baseline assessments. It is anticipated that a total of 100 min–120 min will be required to complete all post intervention and end point assessments.

#### 2.8.4. Biological Sampling 

Before all three assessments ten mL of blood samples will collected by phlebotomists one or two days prior to the administration of questionnaires as per the convenience of participants to measure fasting glucose, complete blood count, lipid profile, cortisol, CRP and biomarkers in the morning hours (empty stomach) between 6.30 a.m.–7.30 a.m. by visiting participants home. A 5 mL post prandial blood sample will be collected after two hours of eating a meal between 1:00 p.m.–3:00 p.m. by visiting the participant’s home. The sample will be collected in EDTA, plain, fluoride vial and will be immediately transferred under a cold chain condition to the central research laboratory of R.D. Gardi Medical College for further analysis. Three mL of sample will be stored in −20 degrees for further analysis of biomarkers. Standard methods will be used for the analysis of samples.

### 2.9. Follow-Up Visits

All the participants will be weekly followed up from the first week to the 36th week. Participants who will miss any session will be telephonically contacted on the same day by research assistants to enquire about the reason for nonattendance. Participants who will not attend a session due to health reasons will be visited by research assistants on the same day to document the events. Additionally, all participants will be visited physically by research assistants at home once a week to document adherence (home exercise/yoga), any self-modification in intervention, health-seeking behavior and to record any adverse events in pre-designed follow-up form (Figure 2). 

### 2.10. Data Management

The principal investigator and study coordinator will be responsible for data management, record keeping, safety and timely backups. Data will be collected in a confidential participants case report form (CRF), which will be later transferred into electronic form (Microsoft Excel). Each participant will be given a unique participation information number (PIN) to de-identify the study participant and to ensure patient anonymity and data confidentiality. The entered data will be transferred to appropriate statistical software for further analysis.

### 2.11. Community Advisory Board

An independent community advisory board (CAB) will be formed to monitor the interventions. The board will comprise of community members including a trained health professional, physical exercise trainer and retired college professor who will hold discussions with the study participants about the process, interventions and other related issues. They will also provide participants’ feedback to the project team. The project team will inform the CAB about any adverse events and the action taken.

## 3. Statistical Analyses

We will use appropriate parametric (*t*-test and Analysis of variance (ANOVA) and non-parametric (Mann–Whitney U and Kreskas Wallis test) tests to compare the socio-demographic-economic and other base-line characteristics of the two groups. Intention-to-treat (ITT) analyses to examine the effects of the intervention that will be explored using mixed linear modeling, in which group × time interactions will be reported with regression estimates, confidence intervals and effect sizes. Sensitivity analyses will also be performed. The moderating effects of gender and age and the interaction effects of education on cognitive outcomes will be also be examined. A similar plan will be followed for the analysis of secondary outcomes.

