### 1.2. Study Objective

This randomized controlled trial will (1) examine the effects of a 12-week yoga based intervention focused mainly on physical postures and movements on subjective well-being among healthy but physically inactive elderly Indian aged 60–80 years and(2) study the effect of a yoga based program on multiple secondary health outcomes affecting elderly. The comparison group with equivalent duration will be light exercise focusing on conventional stretching and mobility.

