#### 2.7.3. Sample Size

The calculation of sample size for this study is based on the effect size reported in a six month long RCT where results of Iyenger yoga on elderly was compared with walking [42]. Based on this study we anticipate that the mean difference (effect size) of around 0.2 on our primary outcome that is well-being in yoga intervention group compared to exercise group. With 80% power, two-tailed significance for the primary between-group comparisons and 1:1 allocation, a total sample of 120 participants is estimated. Assuming a 6-month dropout rate of 20% [72], the total number of participants required at baseline will be 144.

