#### 2.7.5. Randomization and Blinding

The randomization sequence by gender will be generated by an external statistician who is not directly involved in the implementation of the intervention. Each allocation sequence will be transferred into separate sealed envelopes by an assistant nominated by the statistician, which will not be part of the study. Immediately after baseline assessments, the allocation sequence in a sealed envelope will be opened by the principal investigator or project coordinator together with eligible participants. Participants will be informed whether they are allocated to the yoga or light exercise group. At baseline, participants will be requested to not discuss their treatment allocation with the research team responsible for conducting follow-up assessments where a different set of research team blinded to the participant’s allotted group will conduct these assessments. The allotted group will be kept confidential and will be un-blinded only if participants withdraws or due to adverse events. The instructors will also be informed about the allotted group for proper management of yoga/exercise classes.

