## 4. Discussion

With this study we aimed to explore whether the effects of yoga-based intervention differ from those of light exercises in community elderly individuals in an Indian setting. Eligible participants will be individually randomized (after completing baseline assessment) to either 12-weeks of intervention of either a supervised yoga-based program or light exercises. Participants will be allocated to permuted blocks to achieve a gender balance in the two groups. The randomization procedure will be performed externally using a random number generator.

A systematic review concluded that studies of yoga lack clinical evidence [74]. We anticipated our trial would contribute to the current evidence on the effects of yoga interventions on various components of physical and mental well-being. Through this trial, we assumed that comparison of yoga and light exercise focusing on conventional stretching to improve mobility groups will document changes in the outcomes measured such as well-being, mobility, depression, pain, sleep quality and physical activity. We will minimize the barriers to learning and practice among participants and instructors by ensuring a small age gap between participants and instructors; hence, participants will feel less hesitant in following the classes. This may prove to be a comfortable and suitable setting compared to conventional yoga/fitness classes.

Previous studies of effectiveness of yoga have investigated some of the outcomes that will be measured in our study [14,75], however, measuring a range of relevant and meaningful outcomes (as primary and secondary outcomes) simultaneously may provide credible evidence to assess if yoga is more beneficial than light exercises. For elderly, yoga may provide a broad range of healthcare benefits for the mind and body. Yoga may be practiced to maintain health, reduce particular symptoms commonly associated with skeletal pain, and assist in pain relief, and enhance well-being [31,76,77]. We anticipate that practicing yoga may improve subjective well-being and mental health and may result in significant improvement in depression, pain and sleep quality. Furthermore, regular yoga practice can increase mindfulness of the body state and can restore the mind–body balance among elderly people [48,78,79]. The intervention may encourage participants to develop further interest in continuing the physical activity even after the completion of the study.

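### Group × time interactions are the reported effect, with no baseline adjustment or gender-stratum term stated; adding both would gain precision at no cost

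*Protocol article*

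**What the plan says.** Section 3 (Statistical Analyses) of the protocol article plans an intention-to-treat analysis by "mixed linear modeling, in which group × time interactions will be reported with regression estimates, confidence intervals and effect sizes". The same plan is to be followed for secondary outcomes. Gender appears in that section only in this sentence: "The moderating effects of gender and age and the interaction effects of education on cognitive outcomes will be also be examined". The section does not state how baseline is handled, how time is coded, or which covariates enter the main model. It does mention sensitivity analyses, without detail.

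Outcomes are measured at weeks 0, 12+1 and 36+1 (sections 1.5 and 2.8.1). Section 1.2 sets the objective as to "examine the effects of a 12-week yoga based intervention focused mainly on physical postures and movements on subjective well-being", while section 2.8.1 calls week 36 the end point. No section names either visit as primary.

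On allocation, section 2.7.5 says "The randomization sequence by gender will be generated by an external statistician", and section 4 adds "Participants will be allocated to permuted blocks to achieve a gender balance in the two groups". Sections 2.7.5, 2.8.2 and 4 all place randomisation after the baseline assessment.

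**The concern.** Section 3 does more than name a class of model: it fixes the effect to be reported. For a group × time interaction to carry the treatment effect, baseline must be one of the responses. If only weeks 12 and 36 were responses, the interaction would be the difference between the effects at those two visits. With baseline as a response and its mean free in each arm, the week-12 interaction is the difference between arms in mean change from baseline.

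That contrast uses the baseline score inefficiently. Because baseline precedes randomisation, the true difference between arms at week 0 is zero by design. A model that uses this fact, by adjusting for baseline or constraining the baseline means to be equal, estimates the same effect with a smaller standard error. Gender raises a similar but smaller issue: allocation is balanced within gender, but the analysis gives gender only a moderating role.

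At stake is precision in a trial planned on a small effect, from data it already intends to collect.

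**Working it through.** **Inputs.** From section 2.7.3: "mean difference (effect size) of around 0.2 on our primary outcome", 80% power, two-tailed test, 1:1 allocation, 120 evaluable participants (60 per arm). Assumed, because the document does not give them: two-sided alpha 0.05; 0.2 read as a standardised difference (SD 1); equal variance at each visit; complete data; and r, the correlation between baseline and follow-up scores, shown over 0.3 to 0.9. That baseline precedes randomisation is taken from the text of sections 2.7.5, 2.8.2 and 4; Table 1, as extracted, ticks allocation under enrolment.

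**The plan's own figure.** With these inputs and variance 1, n per arm = 2 × (1.960 + 0.842)² / 0.2² = 393, or 786 in total. The stated 120 is not reproduced. It can be reached only with assumptions the article does not state. That is a separate matter, but it shows that there is no precision to spare.

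**Variance of the two estimates.** Per arm, in units of SD²:
- difference in mean change: 2(1−r)
- baseline-adjusted difference: 1−r²
- ratio: (1−r²) / [2(1−r)] = (1+r)/2, a reduction of (1−r)/2

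In the table, each arrow runs from the change-score to the adjusted estimate, for a standardised effect of 0.2.

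| r | Change | Adjusted | Ratio | Reduction | Power, 60 per arm | Total N for 80% power |
|---|---|---|---|---|---|---|
| 0.3 | 1.40 | 0.91 | 0.65 | 35% | 15% → 21% | 1100 → 716 |
| 0.5 | 1.00 | 0.75 | 0.75 | 25% | 19% → 24% | 786 → 590 |
| 0.7 | 0.60 | 0.51 | 0.85 | 15% | 29% → 34% | 472 → 402 |
| 0.9 | 0.20 | 0.19 | 0.95 | 5% | 69% → 71% | 158 → 150 |

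At r=0.5 the difference detectable with 80% power and 60 per arm is 2.802 × √(2 × 1.00/60) = 0.51 SD for change and 2.802 × √(2 × 0.75/60) = 0.44 SD adjusted. The gain is worth 120/0.75 = 160 completers in place of 120.

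**Check by simulation** (60 per arm, three visits, r=0.5, 150 runs, categorical time). With free baseline means, the group × week-12 coefficient equalled the difference in mean change to machine precision, with mean standard error 0.183. With baseline means constrained equal, the mean standard error was 0.158. The variance ratio was 0.75, as the formula predicts.

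**Coding of time.** With categorical time, the model above gives a separate week-12 estimate. With time as linear weeks, the visits 0, 12 and 36 centre at −16, −4 and 20, with sum of squares 672. For a true effect D at week 12 and kD at week 36, the fitted 36-week change is 36 × (−4 + 20k)D/672. This is −0.21D if the effect is gone by week 36 (k=0), zero if 20% remains, and +0.32D if half remains.

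**Gender.** The document gives no association between gender and well-being, so the gain from a stratum term cannot be computed.

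**The case against.** The strongest reply is that section 3 is silent rather than wrong. It does not say that baseline or gender is left out, and a condensed article may leave covariates, baseline constraint and time coding to a fuller document. A mixed model with a common baseline mean also reports group × time coefficients, and it has the full precision of baseline adjustment. All of this stands. A reader might infer that the trial will be analysed without adjustment; the text does not establish that.

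A reader might also infer that the model cannot isolate a 12-week effect, or could reverse its sign. Neither is supported. Three discrete visits, and interactions in the plural with estimates and intervals, fit categorical time at least as well as any other coding, and categorical time yields the week-12 effect directly. The sign reversal needs linear weeks, which no section states or excludes, together with an effect that has largely faded by week 36. Nor can the model be faulted for missing week 12 as the primary visit, since no section makes it primary.

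On gender, the moderation analysis would ordinarily include a gender main effect, and omitting it from the main model errs on the conservative side.

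What remains is that the article chose to state its effect measure. In its ordinary form that measure is less precise than an available alternative that needs no further data.

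**Conclusion.** The point holds as a free improvement, not as an error that biases the result. In the usual model with unconstrained baseline means, the reported interaction is unbiased under randomisation, but its variance can be cut by 35% at r=0.3 down to 5% at r=0.9. These figures rest on an assumed r, equal variances and complete data. The loss disappears if the trial team already intends a common-baseline model, which the text permits. The effect of omitting the gender stratum is probably slight and cannot be quantified here.

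The gain should not be read as a remedy for the sample size. At a standardised effect of 0.2 with 60 per arm, power stays below 80% at every r examined, with or without adjustment.

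**What to change.** In section 3, specify for each well-being scale a mixed model with time as a categorical factor, the baseline score as a covariate (or baseline as a response with its means constrained equal across arms), and gender as a fixed term. Report the adjusted yoga-minus-exercise difference with its 95% confidence interval at each of weeks 12+1 and 36+1, and have the sponsor name which of the two is primary. If baseline becomes a covariate, the quantity to report is the group difference at each visit, because the group × time term then no longer measures the treatment effect. Keep the gender and age moderation analyses as exploratory.

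The cost is a change of analysis wording. No new data, visits or participants are needed.

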### 3.1. Assessment of Adverse Events

In the proposed study, the potential risks of adverse events are minimal. Most frequently anticipated adverse events are muscle strains, soreness, knee pain, Achilles tendon, back spasms, neck pain, vertigo, migraine and reoccurrence of prior lower back pain or shoulder problems [73].All sessions will be conducted by qualified yoga instructors at a health center or near a health center in Ujjain. Participants will be provided access to emergency medical care at all times. The interventions will be specially designed for elderly. A team of physicians will screen all potential participants and will exclude those with health problems that may hinder participation..All adverse events will be recorded, and followed up by research assistants. Adverse events will be formally assessed during the weekly home visits of study participants where participants will be asked to inform project team of any health related events they encountered in past week. Adverse events will also be communicated to the team of physicians for assessments and medical management.

### 3.2. Ethics Approvals

The study will be conducted in accordance with the protocol, Good Clinical Practice as well as the requirement from the Institution’s Ethical Committee. The study is approved by the institutional ethics committee of R.D. Gardi Medical College, Ujjain (IEC Ref. No.-09/2018). The study is also registered in CTRI (Clinical Trials Registry India) Indian Council of Medical Research (CTRI/2018/07/015051).

## 4. Discussion

With this study we aimed to explore whether the effects of yoga-based intervention differ from those of light exercises in community elderly individuals in an Indian setting. Eligible participants will be individually randomized (after completing baseline assessment) to either 12-weeks of intervention of either a supervised yoga-based program or light exercises. Participants will be allocated to permuted blocks to achieve a gender balance in the two groups. The randomization procedure will be performed externally using a random number generator.

A systematic review concluded that studies of yoga lack clinical evidence [74]. We anticipated our trial would contribute to the current evidence on the effects of yoga interventions on various components of physical and mental well-being. Through this trial, we assumed that comparison of yoga and light exercise focusing on conventional stretching to improve mobility groups will document changes in the outcomes measured such as well-being, mobility, depression, pain, sleep quality and physical activity. We will minimize the barriers to learning and practice among participants and instructors by ensuring a small age gap between participants and instructors; hence, participants will feel less hesitant in following the classes. This may prove to be a comfortable and suitable setting compared to conventional yoga/fitness classes.

Previous studies of effectiveness of yoga have investigated some of the outcomes that will be measured in our study [14,75], however, measuring a range of relevant and meaningful outcomes (as primary and secondary outcomes) simultaneously may provide credible evidence to assess if yoga is more beneficial than light exercises. For elderly, yoga may provide a broad range of healthcare benefits for the mind and body. Yoga may be practiced to maintain health, reduce particular symptoms commonly associated with skeletal pain, and assist in pain relief, and enhance well-being [31,76,77]. We anticipate that practicing yoga may improve subjective well-being and mental health and may result in significant improvement in depression, pain and sleep quality. Furthermore, regular yoga practice can increase mindfulness of the body state and can restore the mind–body balance among elderly people [48,78,79]. The intervention may encourage participants to develop further interest in continuing the physical activity even after the completion of the study.

The present understanding came from mainly studies conducted in residential care homes [80]. Most of other studies did not included elderly. There is a requirement of well-designed community-based follow studies to assess long term changes and outcomes. We feel that with yoga being a practical, easy and feasible exercise that it can help in emotional and physical betterment and ultimately wellbeing in an elderly group. This project aimed to encourage participants to initiate and continue a yoga-based activity after study completion. We anticipate significant improvements in several health domains. The intervention would benefit participants, their families and society in terms of (anticipated) lower health costs. Moreover, the study results may be of broader use in other settings. We would use the standardized measurements and blinded follow-up assessments, to reduce the assessment bias.

However, there may be some possible limitations in this study. This study concerns with the overestimation of intensity/duration of physical activity assessed through subjective measurement, due to social desirability of responses i.e., there is a possibility that contact with other participants/trainers/research assistants may increase wellbeing in studied population. Generalizability of study will be limited to similar settings and conditions. We will recruit only those individuals that will show interest towards devoting time in physical activities.

## Figures and Tables

**Figure 1 geriatrics-04-00064-f001:**
[figure not shown]
Design and participant flow chart according to SPIRIT 2013 guidelines (Standard Protocol Items: Recommendations for Interventional Trials).

**Figure 2 geriatrics-04-00064-f002:**
[figure not shown]
Follow up flowchart.

**Table 1 geriatrics-04-00064-t001:** Schedule of enrolment, interventions and assessments, according to SPIRIT 2013 guidelines. BMI, body mass index; SPIRIT, Standard Protocol Items: Recommendations for Interventional Trials; WHR, waist-hip ratio, TNF-α, Tumor necrosis factor alpha; IL-6, Interleukin6; CRP, C-Reactive Protein.

Study Period						
**Time Point**		**Enrolment**	**Baseline**	**Intervention**	**Post Intervention**	**Endpoint**
		week −1	week 0	week 1–12	week 12+1	week 36+1
**Eligibility Screen**		✓				
Informed Consent		✓				
Allocation		✓				
